### Study design

The study will be conducted as a three-armed randomized controlled trial including two intervention groups and one control group (CG) (Fig. 1, study design and flow of participants). Intervention activities will be completed as either whole-body movements (WM, intervention group I) or hand movements (HM, intervention group II) over an 8-week period at four primary schools. Using random selection of sealed envelopes, participants will be randomized stratified by class in an approximate 1:1:2 fashion to either WM, HM or CG. Specifically, within each class six subjects will be assigned to WM, six subjects to HM, while the remaining subjects will constitute the CG. The project leader will be responsible for all steps related to the enrollment and allocation of participants. Outcome measurements will be collected before and after the intervention period enabling assessment of the intervention effects. A schematic diagram of time schedule of enrolment, interventions and assessments are presented in Table 1.

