### Justification of sample size

The study has not been formally powered based on results from a specific study, as no equivalent study with similar outcomes exists. In general, the effects of physical activity lessons are observed to be small to moderate [60]. In addition, a study based on the embodied learning theory found small to moderate effect sizes in regards to letter knowledge when comparing learning activities involving whole-body movements with visual learning activities [4]. Given three groups with an equal number of participants in each group, power calculations suggest that 158 subjects are needed to achieve a power of 80% and a level of significance of 5% for detecting an effect size of 0.25 between groups. Since the control group will include approximately twice as many participants as each of the intervention groups, 212 subjects are needed to detect an effect size of 0.25 (intervention group: *n* = 53, control: *n* = 106). Accounting for a 20% dropout rate or data loss for other reasons, 265 participants will be included in the study. Power calculations have been done using Gpower [27].

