### Outcome measurements

To evaluate the effect of the interventions, tests assessing reading related skills will be administered at the schools prior and post the 8-week intervention period by trained staff. In addition, a third data collection will be completed approximately three months after the cessation of the intervention period to evaluate potential retention effects. Primary outcomes assessing potential training effects include word reading (target words) and knowledge of trained letter-sound correspondences, while secondary outcomes assessing potential transfer effects include word reading (untrained words), letter fluency, general knowledge of letter-sound correspondences and word reading accuracy and speed. In addition, to explore potential mediators working memory, attention, intrinsic motivation, gross motor skills and fine motor skills will be assessed. At baseline, immediately post intervention and at three months follow-up, tests will be administered in groups and individually on two separate days. Compliance data will be collected following each session by the instructor/teacher and intrinsic motivation will be evaluated following four different sessions (week 2, 4, 6 and 8). All data will be collected during school hours which will ensure the children’s participation during data collection. In cases of absence on the day of scheduled data collection, children will be invited to complete the tests on another day.

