### Plan for data analysis

In accordance with the Consolidated Standards of Reporting Trials (CONSORT) 2010 for randomized controlled trials [57], flow of participants will be reported. Descriptive statistics will be summarized across schools and classes for each group. Potential differences at baseline between subjects included and excluded in the analyses (e.g. drop-outs) as well as differences between groups at baseline will be tested. Further, compliance to the intervention will be summarized for each group. Intention-to-treat analyses will be performed to assess the effect of the intervention on primary as well as secondary outcomes. Multilevel mixed model will be used as this model is able to provide an unbiased estimate given missing data assuming data is missing at random conditional on variables included in the model [83]. Patterns of missing data will be investigated. To account for the cluster structure in the data (i.e. subjects within classes within schools), class and school will be included as random effects in the model. Due to the randomized design, which is used to ensure equal distribution of confounding variables between groups, we will only adjust for potential confounding variables (e.g. sex, age) which show unevenly distribution between groups at baseline. In addition, per protocol analyses will be conducted using above-mentioned approach including participants with a participation rate above 90%. In addition, structural equation models (SEMs) will be used for mediation analyses to explore potential mediators.

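### Covariates enter the outcome models only if they look unbalanced at baseline, with no threshold or closed list; a fixed set should replace this rule, and the role of the baseline score should be stated

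*Protocol article*

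**What the plan says.** The section Plan for data analysis states that "differences between groups at baseline will be tested", and that, because the groups are randomised, "we will only adjust for potential confounding variables (e.g. sex, age) which show unevenly distribution between groups at baseline". Sex and age are examples; no full list and no criterion for uneven is given. The other model terms are stated as "class and school will be included as random effects in the model". The mixed model is justified as unbiased "assuming data is missing at random conditional on variables included in the model". The per-protocol analyses are to follow the same approach.

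On the baseline scores, Study design says "Outcome measurements will be collected before and after the intervention period enabling assessment of the intervention effects", and Outcome measurements says "At baseline, immediately post intervention and at three months follow-up, tests will be administered in groups and individually". Neither section says how the baseline score enters the model: as a covariate, as one of the repeated responses, as part of a change score, or not at all.

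**The concern.** This is a stated rule, not a detail left for later, and it is badly fixed in three ways.

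- **Wrong criterion.** Children are randomised within class, so a baseline test examines a null hypothesis that is true by design. What makes a covariate worth including is how well it predicts the outcome, not whether it differs by chance. The Background section itself calls phoneme awareness and letter knowledge before formal instruction unique predictors of later reading and spelling.
- **Open choice.** Without a threshold or a closed list, the covariates are settled only after the baseline data are seen, for every primary and secondary outcome and again per protocol. The Blinding section promises a blinded analyst. Yet the project leader runs the analyses (Ethics and data security) and is also responsible for allocation (Study design), which is a further reason to close the choice in advance.
- **Missing data.** The missing-at-random claim is conditional on what is in the model. If that content depends on observed balance, the assumption is not fixed either.

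At stake are power and a fully prespecified primary model.

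**Working it through.** **Inputs from the protocol article (Justification of sample size).** Power 80%, significance level 5%, effect size 0.25; 158 children with equal groups; 53 / 53 / 106 = 212 at 1:1:2; 265 after 20% dropout.

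**Assumptions, not in the documents.** Baseline-post correlation r = 0.3, 0.5 or 0.7; standardised difference d = 0.35 for one intervention arm against control; imbalance judged by p < 0.05; two-sided 5% tests; normal scores; no clustering.

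**1. The plan's own figure.** A three-group F test with f = 0.25 has power 0.7995 at N = 157 and 0.802 at N = 158. Then 158/3 rounds up to 53, 4 × 53 = 212, and 212/0.8 = 265. The stated sizes reproduce and take no credit for baseline correlation. They are not in error on this point.

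**2. How often the rule would act.** With k independent covariates, the chance of at least one flag in one comparison is 1 − 0.95^k: 10% (k = 2), 23% (k = 5), 40% (k = 10). Any single covariate is flagged in about 5% of trials, so a prognostic covariate governed by the rule is nearly always left out.

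**3. Three readings for the baseline score.** With unit variance, SE = √(v × (1/53 + 1/106)) = 0.1682 × √v, where v is
- 1 if the score is left out,
- 2(1 − r) for a change-type contrast,
- 1 − r² for fixed adjustment (in complete data, a longitudinal model with a common baseline mean gives essentially the same).

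The ratio d/SE is 0.35/0.1682 = 2.08 with the score left out. With fixed adjustment it is 2.18, 2.40 and 2.91 at r = 0.3, 0.5 and 0.7. With the change-type contrast it is 1.76, 2.08 and 2.69. Power from the t distribution, with the conditional rule by simulation:

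| Analysis | r = 0.3 | r = 0.5 | r = 0.7 |
|---|---|---|---|
| Score governed by the conditional rule | 54% | 55% | 55% |
| Change-type contrast | 42% | 54% | 76% |
| Fixed baseline adjustment | 58% | 67% | 83% |

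With the score never adjusted for, power is 54% at every r. Simulation runs differ by about a percentage point.

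**4. Other effect sizes (50,000 simulated trials each).** At d = 0.25 the rule has power 31% (r = 0.5) and 32% (r = 0.7), against 40% and 54% with fixed adjustment. At d = 0.5 the figures are 85% and 86%, against 92% and 98%.

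**5. False positives.** Under no effect, the rule applied to the baseline score rejects in about 4.6%, 4.2% and 3.7% of trials at r = 0.3, 0.5 and 0.7. This is below 5%.

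**The case against.** A reader might infer that the rule covers the outcome's own baseline score, so that the strongest predictor is normally dropped. The text does not support that as a fact. It speaks of potential confounders and names only sex and age. Outcomes are measured before and after the intervention, reading tests have three time points, and a mixed model is planned; a repeated-measures model that already uses the baseline score fits this equally well. In a condensed article, silence on how that score enters is not in itself a fault. This stands, and it makes the power figures conditional on the reading.

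The correlation is also unknown. Participants and recruitment says few children can read words at the start of Grade 0, so a floor effect may weaken r for word reading, one of the two primary outcomes. The untrained-word test uses two matched versions, so not every outcome is measured with an identical test. For sex and age alone no gain has been computed, and it is probably smaller.

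A reader might also infer that the rule inflates false positives. It does not: the simulated error is conservative, and the trigger uses baseline data, not outcomes.

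None of this removes the stated rule: selection by observed imbalance, with testing and no threshold or closed list.

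**Conclusion.** The point holds for what the section fixes. Covariates are chosen by observed imbalance rather than prognostic strength, and the model stays open until baseline data are seen.

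Under the assumptions above, moving to fixed baseline adjustment at d = 0.35 gains
- about 4, 12 or 28 percentage points of power (r = 0.3, 0.5, 0.7) if the score would otherwise be left out or governed by the rule;
- about 16, 13 or 7 points if a change-type contrast would otherwise be used;
- nothing further from the baseline score if a common-baseline model is already intended. The open choice over sex, age and other covariates then remains.

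Fixed adjustment is at least as good under every reading, but its size rests on r, on the reading and on ignoring clustering and floor effects. The sample size is not wrong and the error rate is not inflated. This is a should-fix, not a threat to the validity of the trial.

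**What to change.** Replace the conditional rule in Plan for data analysis. Every primary and secondary outcome model, including the per-protocol analyses, should contain the baseline value of that outcome, age and sex as fixed covariates regardless of observed balance. A longitudinal model with a common baseline mean across arms, plus age and sex, serves equally. For the untrained-word test, use the score on the version taken at baseline.

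Drop significance tests of baseline differences between the randomised groups and show descriptive values only. The planned comparison of children included in and excluded from the analyses is a separate matter and can stay.

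The cost is about two sentences, settled before the data are analysed. The baseline tests are already scheduled, so no further data collection is needed for the baseline scores.

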#### Compliance to the intervention

Teachers/instructors will be asked to keep a written log of attendance of each child. Specifically, data on 1) presence (yes/no), and 2) active participation (yes/no) will be registered. Moreover, teachers/instructors will note whether each session has been completed (yes/no) and to what degree it followed the protocol (scale 1–5).

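### The per-protocol analysis inherits a covariate rule justified only by randomisation, although its children are selected after randomisation

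*Protocol article*

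**What the plan says.** All of this stands in the protocol article under Plan for data analysis. The main analyses are intention-to-treat, by a multilevel mixed model with class and school as random effects. The covariate rule and its reason are given together: "Due to the randomized design, which is used to ensure equal distribution of confounding variables between groups, we will only adjust for potential confounding variables", with sex and age as examples, and only those "which show unevenly distribution between groups at baseline". No other reason for restricting adjustment is offered.

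The next sentence sets the second analysis: "per protocol analyses will be conducted using above-mentioned approach including participants with a participation rate above 90" per cent. No separate covariate set, weighting or other provision is given for that subset.

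The section also plans baseline comparisons: "Potential differences at baseline between subjects included and excluded in the analyses (e.g. drop-outs) as well as differences between groups at baseline will be tested". It does not say that balance is examined again within the per-protocol set.

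**The concern.** Randomisation balances confounders, in expectation, among all children randomised. It gives no such assurance for a subset chosen by what children did afterwards. The plan nevertheless carries over, unchanged, the rule that rests on that assurance. This is a rule the article states, not a detail left for a later document.

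Unequal selection by arm is conceivable. Trained instructors run the movement sessions and the usual teachers run the control sessions, and these same people keep the participation log (Structure and learning content of the activities; Compliance to the intervention). The Discussion accepts that the difference in deliverers may itself produce differences between groups. If children with stronger early skills are more likely to pass the cut, and the arms pass different shares, the retained groups differ in baseline skill. That difference then enters the per-protocol contrast unless the model conditions on it. What is at stake is the reading of the per-protocol result beside the intention-to-treat result: a gap between the two could be selection rather than a dose effect.

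**Working it through.** The plan gives no figure on this point, so the size below is illustrative.

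**Inputs from the article**
- 24 sessions; cut above 90%.
- 53 children per intervention arm and 106 controls (Justification of sample size). These agree with the stated totals: 53 + 53 + 106 = 212, and 212/0.80 = 265.

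**Assumed inputs (not in the article)**
- Share passing the cut: 70% of controls, 88% of a movement arm.
- Correlation ρ between a latent participation tendency and baseline skill: 0.2, 0.3 or 0.4, the same in each arm.
- Correlation between baseline and outcome: 0.6. No true arm effect.

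**Step 1: what the cut demands.** 0.90 × 24 = 21.6, so a child needs at least 22 sessions and may miss at most two. With independent absences, P(at most 2 missed of 24) is 88.4% at 5% absence and 69.9% at 8%. The assumed shares therefore correspond to a three-point difference in non-participation.

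**Step 2: baseline gap after selection.** If a fraction p is retained above a cut z = Φ⁻¹(1 − p), the retained children's mean baseline is ρ·φ(z)/p in SD units.
- Control, p = 0.70: z = −0.524, φ(z) = 0.3477, ratio 0.4967.
- Movement, p = 0.88: z = −1.175, φ(z) = 0.2000, ratio 0.2273.
- Difference: 0.4967 − 0.2273 = 0.2694. The gap (control higher) is 0.2694ρ.

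**Step 3: bias and chance of detection.** Unadjusted post-score bias = 0.6 × gap. With 0.70 × 106 = 74.2 and 0.88 × 53 = 46.6 children retained, the standard error of the baseline difference is √(1/74.2 + 1/46.64) = 0.187 SD, taking the SD within the retained set as about 1. The chance that a two-sided 5% test flags the gap is 1 − Φ(1.96 − gap/0.187) + Φ(−1.96 − gap/0.187).

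| ρ | Baseline gap (SD) | Post-score bias (SD) | Chance flagged |
|---|---|---|---|
| 0.2 | 0.054 | 0.032 | 6.0% |
| 0.3 | 0.081 | 0.048 | 7.2% |
| 0.4 | 0.108 | 0.065 | 8.9% |

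The detection rate is barely above the 5% expected with no imbalance at all.

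**Step 4: effect of adjustment.** Conditioning on the baseline score brings the bias to about 0.00 SD. This follows from the set-up, because here selection depends on outcome only through baseline. It does not show that adjustment would remove everything in practice.

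**Step 5: sensitivity**
- If the share retained and its dependence on baseline skill are the same in both arms, the bias is zero.
- Under stronger assumed selection (85% v 55% retained with a log-odds slope of 0.5 or 1 per SD in both arms; or 70% in both arms with a slope of 0 in one and 0.5 or 1 in the other), the baseline gap is 0.14 to 0.25 SD. The bias is then 0.07 to 0.18 SD at a baseline-outcome correlation of 0.5 to 0.7, and the test flags the gap 11 to 24% of the time.
- If change scores are analysed, the bias is (0.6 − 1) × gap = −0.4 × 0.054 to −0.4 × 0.108, or −0.02 to −0.04 SD: smaller and of opposite sign.

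**The case against.** The strongest reply is that arm-differential selection is not shown. Children are randomised within class, the arms run at the same schools and the control sessions run in parallel, so absence from school should fall on all arms alike. This stands as a limit: bias needs selection that differs by arm, and the article gives no figure for that.

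Second, the article does not say that baseline is left out of the mixed model. Outcomes are measured before and after, and a model that conditions on the baseline score would remove the modelled bias. That is fair, but the article does not commit to such a model; the only covariate rule it states is the conditional one.

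Third, the reused approach may be read as repeating the imbalance check within the per-protocol set, and included and excluded children are to be compared. Even on that reading, the check has little power at these numbers.

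Fourth, the analysis is additional to intention-to-treat. This stands and limits the point's weight.

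A reader might go further and infer that children qualify on attendance alone, whether or not the programme was delivered. The text does not support this. It speaks of a participation rate without saying how it is built, and the log holds more than presence: "data on 1) presence (yes/no), and 2) active participation (yes/no) will be registered". A condensed article may leave the construction of that rate to a fuller document. A reader might also want only sessions logged as completed to count, since "teachers/instructors will note whether each session has been completed (yes/no"). But Table 1 lists completion at group level. With at least 22 of 24 sessions needed, three incomplete sessions would remove every child in that class's arm (six movement children or about twelve controls), and could itself create unequal selection. That is a debatable trade-off, not a correction the documents call for.

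**Conclusion.** The point holds in a narrow form. The reason given for restricting covariates does not extend to a set formed after randomisation, and the check that would trigger adjustment would seldom detect an imbalance of the size considered. The resulting bias is possible, not certain. It is about 0.03 to 0.06 SD on unadjusted post scores under the assumed 70% v 88% retention and correlations, larger if selection is stronger, zero if selection works alike in all arms, and reversed in sign for change scores. Every retention share and correlation behind these figures is an assumption. The intention-to-treat analyses of the primary and secondary outcomes are unaffected, so this is a minor improvement to a secondary analysis.

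**What to change.** Replace the carried-over covariate rule for the per-protocol analysis with wording such as: the per-protocol model keeps the class and school random effects and always includes the baseline score of the outcome, age and sex, whatever the baseline comparison shows; it is reported as a supportive, non-randomised comparison, with a note that confounding by unmeasured factors may remain.

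The cost is about two sentences. Baseline scores are already scheduled for the reading outcomes, sex is on the background form, and age is already named as a possible covariate. The participation cut itself need not change.

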### Ethics and data security

The study is approved by The Faculty of Sciences Ethical Commitee at University of Copenhagen (#504–0032/18–5000). Before inclusion, all parents with children attending preschool at the included schools will receive written and oral information provided by the project leader. For a child to participate, written informed consent must be returned to the project leader by the parents/legal guardian prior to the baseline measurements (standard form S5, cf. https://www.nvk.dk/samtykkeerklaeringer). Participation in the study may be discontinued at all times with no obligation to provide a reason. To anonymize the data, each child will be provided with an identification number (ID number), and no participant identifying information will be stored alongside data. A transfer key coupling the ID number with personal information will be safely stored separately from the trial data in order to secure confidentiality. All rules from the Danish Data Protection Agency and General Data Protection Regulation (GDPR) will be followed during all phases of the PLAYMORE study. Analyses will be conducted by the project leader, who is not practically involved in the data collection or the completion of the intervention/control. In order to promote data quality, independent research assistants will complete double data entry. The results will be published in peer-reviewed journals and through presentations at international scientific conferences. Authorship will be in agreement with The Vancouver Recommendations.

## Discussion

The PLAYMORE study will provide additional insight into the effects of physical activity/movement on academic performance. Although, PA has previously been linked to reading performance, the evidence is inconclusive [3, 22, 51, 71] and only few experimental studies have previously investigated the effects of movement integrated into reading practice (i.e. based on principles of embodied learning) [4, 52]. Moreover, the potential influence of motor modality (e.g. hand movement vs. whole-body movements) is still unclear.

Within educational research concerning embodied learning, intervention studies are characterized by a wide variety of approaches differing in regards to e.g. motor modality, level of bodily engagement, task integration and congruency between movement and learning task [73]. Consequently, to enable a fair comparison between studies, thorough descriptions and characterizations of activities included in the different intervention studies are essential. Also, aspects that should be considered and discussed when characterizing embodied learning activities are the level of task integration, the level of bodily engagement [73] and congruency (i.e. congruency between the movement and the learning task) [40]. The two PLAYMORE interventions involve activities with a close temporal and meaningful coupling between the movements and the learning task, thus representing activities with a high level of task integration. However, the different activities (see Table 3) vary in regards to congruency between the movement and the learning task. Accordingly, activities range from “*Letter sound*” (i.e. activity II, Table 3) and “*Symbol-Sound Coupling*” (i.e. activity III, Table 3) representing a high level of congruency between movement (e.g. drawing the letter form/symbol while linking to a specific sound-movement coupling in which the movement and sound have similar characteristics) and learning task (i.e. coupling between letter form/symbol and sound) to “*Rhyme Twister*” (i.e. activity VII, Table 3) representing a low level of congruency between the movement (e.g. placing hand/feet on two rhyming words) and the learning task (i.e. rhyming, identifying similar sounds). Even though, it is recommended that congruency should be considered in the design of embodied learning interventions, the contribution of this factor to the effectivity of embodied learning activities is uncertain [73].

According to the taxonomy suggested by [73] the activities in the two PLAYMORE interventions may be characterized differently in regards to the level of bodily engagement, which may lead to different effects of the two interventions [73]. Skulmowski and Rey argue that a higher level bodily engagement may not automatically cause increases in learning performance (see [82] for a related discussion). However, in the embodied learning research, only few studies have previously compared the effects of part-body movements (e.g. hand movements) with effects of whole-body movements on subdomains of academic performance [5, 53], and neither of them focused on early reading skills in children. Thus, the inclusion of two intervention groups performing either part-body movements (i.e. arms and hands) or whole-body movements, respectively, will provide valuable information in regards to the influence of level of bodily engagement. Besides advancing our understanding of the relationship, this information will be of particular relevance to professionals implementing PA/movement into academic teaching. Compared to whole-body movements, hand movements may seem more practicable (e.g. requires little space, less time consuming) to the majority of teachers with no prior experience in organizing physical activities, and thus, if effective, hand movements may be more feasible to implement in the general school system.

The PLAYMORE study is unique as the methodology is stringent including theoretically founded activities that are well-described. Another strength of the study is the blinding of assessors at baseline and 8-weeks follow-up, thereby limiting the risk of bias. In addition, participants will be blinded at baseline, however, due to the nature of the study, it will not be possible to blind participants during the intervention period or at follow-up, which could introduce bias. However, with the age of the participants in mind, we do not expect this to influence the results significantly. The study includes a highly relevant control group completing the exact same academic content as the intervention groups, enabling a fair comparison between the groups. However, we are aware of the limitations within the control group and that these limitations may introduce bias. Usual teachers will administer the control activities while trained instructors will instruct the intervention activities, which may cause differences (e.g. comfort, newsworthiness) between the groups not associated with the differences in bodily movement. This decision is made for practical and ethical reasons, since it enables children without written consent to participate in the control activities along with their peers. In addition, the children-to-teacher rate is approximately twice as large in the control group compared to the intervention groups, which may affect the group dynamics. However, since teachers/instructors are asked to correct and support on a group level, the differences in children-to-teacher rate will most likely not affect the time spend correcting/supporting each child.

